### Recruitment

Potentially eligible patients identified by the clinician in the initial assessment will be informed about the study and given an information sheet. The clinician will obtain consent from the patient to be contacted by a researcher. If the patient is willing, the researcher will contact the patient and arrange to meet at the clinic or via a Skype™ telephone appointment to provide and discuss further information about the study.

The recruiting researcher will explain the rationale for the study and its design, uncertainties about the effectiveness of the intervention, options available outside of the trial, and the right not to take part in the study or to withdraw at any time up to the analysis. Those willing to take part in the study will be asked to consent to randomization and sign the consent form. If informed consent is subsequently provided, the patient will partake in an assessment. Consent to have guidance sessions recorded will not be required to be included in the trial.

### Randomization

The recruiting researcher will log in to the Web-based automated randomization service/system operated by the UK Clinical Research Collaboration (UKCRC) registered King’s Clinical Trials Unit at the Institute of Psychiatry, King’s College London for the intervention allocation, which will be conveyed to the participant by the recruiting researcher. Allocation will be at the level of the individual, using block randomization with randomly varying block sizes, to preserve allocation concealment. Randomization will be stratified by (1) depression (Hospital Anxiety and Depression Scale; cut-off = 11); (2) severity of disability (SF-36 physical functioning subscale ≤40 and ≥45, which was close to the mean score from all participants in the PACE trial [11]; and (3) by center. This will help to ensure equal proportions of depressed and more severely disabled participants in each treatment arm. Automatic emails will confirm the intervention allocation. If for any reason the randomization service is unobtainable, randomization will be completed during the next working day and the participant will be told of the result by telephone.

### Interventions

#### Standard Medical Care (SMC)

Participants will be informed at the end of their assessment appointment that they have been allocated to SMC and that they should follow the advice of their GP and specialist doctor as usual. They will not have access to the self-help booklet used in the trial. As per usual, specialist doctors will prescribe or advise regarding medication as indicated for symptomatic treatment of associated symptoms (eg, insomnia and pain) and comorbid conditions (eg, depressive illness). These patients will start the therapy to which they have been referred after the endpoint of the trial at 12 weeks or more after randomization, when it becomes available. After completion of trial participation, these patients will also receive a copy of the GES booklet.

#### SMC Plus GES

In addition to receiving SMC, participants in the GES arm will be given a copy of a self-help booklet describing a 6-step program of graded exercise that should take approximately 12 weeks to complete. A physiotherapist will then join the participant for a 30-minute appointment either face-to-face in the clinic or via telephone/Skype™ within 5 working days of randomization. The physiotherapist will explain how the booklet should be used, explain steps 1 to 4 of the booklet, and answer any questions/concerns of participants. The physiotherapist will provide up to 3 further 20-minute telephone or Skype™ support appointments over the next 8 weeks. These 3 follow-up appointments will take place approximately 1 to 2, 4 to 5, and 7 to 8 weeks after the participant’s initial appointment. The physiotherapists will be trained and experienced in delivering GET as a treatment for CFS/ME, and in how to guide and support participants in their use of the booklet without providing additional therapy. The emphasis of guidance/support will be on solutions provided by the booklet and how to apply what is learned, and will follow a support guidance checklist. Contacts with the physiotherapist will be audio-recorded, with informed consent, for training and supervision purposes to ensure that therapists adhere to the guided self-help manual. The GES supervisor will listen to a random sample of the recordings throughout to ensure therapists are maintaining a consistent approach.

*The Guided graded Exercise Self-help (GES) booklet* is based on the approach of GET developed for the PACE trial [11], which was itself based on effective approaches tested in previous trials [9]. GES is also based upon the recommendations made by NICE in 2007 [7]. Patients with CFS/ME attending clinics at St Bartholomew’s and King’s College hospitals in London piloted the booklet. Engaging and encouraging participants to undertake their exercise plans using the GES booklet are cornerstones of the guidance and will be its main focus.

The physiotherapist will use established techniques [28] to maximize engagement and adherence throughout. Participants will be encouraged to approach their graded exercise program using the 6 steps described in the booklet: stabilizing a routine, starting regular stretching, deciding on a goal and choosing a type of physical activity (PA), setting their PA baseline, increasing the duration of PA, and finally increasing the intensity of PA. During each session, the therapist will inquire about progress and answer any questions, with a focus on moving forward to the next step. They will recognize achievements and provide feedback to participants on their efforts, with the aim of increasing motivation and self-efficacy. Near the end of the guidance intervention, the physiotherapist will discuss setbacks. If a participant cannot be contacted by telephone or Skype™, an email will be sent in an attempt to reengage them. After the last guidance session, the physiotherapist will rate the participant’s CGI (health), their adherence to the GES guided support, and their acceptance of the therapy model.

#### Departure from Intended Treatment

To measure departure from intended treatment, participants will be asked at follow-up whether they adhered to the booklet and guidance, and how much PA they undertook in the past week. The number of participants who actively withdraw from either intervention will be recorded. The GES booklet is currently only available from specialist doctors and physiotherapists at specific CFS/ME clinics. For the duration of the trial, the GES booklet will not be available on our websites or patient libraries. Participants who are offered face-to-face therapy before completion of their 12 weeks in the trial, due to an appointment becoming available earlier than expected in the service, will complete their follow-up measures prior to that appointment. This will be considered a “protocol deviation.”

### Assessments and Procedures

#### Criteria for CFS

The research assessment will include evaluation of the operational criteria for the Oxford and Centers for Disease Control and Prevention (CDC) criteria for CFS. Although not eligibility criteria, these will be used in subgroup analyses [1,2]. To determine both excluding and allowable comorbid psychiatric diagnoses, a standardized psychiatric interview (Structured Clinical Interview for DSM-IV Axis I Disorders; SCID) [29] will be conducted by a trained and supervised research assessor.

#### Baseline

The following self-rated inventories will be collected at the first assessment (baseline): 11-item Chalder fatigue questionnaire (CFQ), using Likert scoring [30]; SF-36 physical function short form subscale (SF-36 PF) [31]; Hospital Anxiety and Depression Scale (HADS) [32]; Euroqol Questionnaire (EQ-5D) [33]; Work and Social Adjustment Scale (WSAS) [34]; International Physical Activity Questionnaire (IPAQ) [35]; Tampa Scale of Kinesiophobia-Fatigue (TSK-F) [36]; Client Service Receipt Inventory (CSRI) [37]; and Patient Health Questionnaire (PHQ-15) [38]. Participants will be asked when their CFS/ME started; whether they have ever received GET, CBT, or pacing from a therapist; whether they have ever used any listed self-help resources; and whether they are members of a CFS/ME self-help group. Participants will also be asked about their ethnicity, highest education level, current employment status, whether they have had to reduce/stop work due to their CFS/ME, other health problems, and whether they are taking antidepressant medication for any reason.

#### 12-Weeks Post-randomization

The main outcome end-point will be 12 weeks after randomization, before patients begin their service therapy. We chose 12 weeks as this was about the length of the waiting list for therapy at the St Bartholomew’s CFS service at the time of application for funding. At the end-point, the following information will be collected via questionnaires sent by mail with a stamped addressed envelope: SF-36 PF, CFQ, self-rated Clinical Global Impression of Change (CGI) [39] (this will be done once for overall health and then a second time specifically for CFS), HADS, EQ-5D, WSAS, IPAQ, CSRI, and PHQ-15. Participants will be asked to describe the following: whether they have used any of 4 listed self-help resources since randomization, including the unpublished GES guide [40-42]; how satisfied they are with the help they received; how closely they followed the GES guide; their current employment status and whether they have had to reduce/stop work due to their CFS/ME; any new health problems not already reported; and whether they are taking antidepressant medication for any reason.

#### 12-Months Post-randomization

The primary purpose of the 12-month follow-up will be to obtain the health-economic assessment (see section below); however, we will also collect data on the primary outcome measures and the CGI so that we can assess longer-term physical functioning, fatigue, and change in overall health and CFS. The following information will be collected via questionnaires sent in the mail with a stamped addressed envelope for return: CFQ, SF-36 PF, CGI, EQ-5D, and CSRI.

#### Primary Outcomes

We initially planned to use the SF-36 PF as the primary outcome analyzed as an interval variable collected at 12-weeks postrandomization. The SF-36 PF is scored as the sum of responses to 10 items related to functioning on everyday activities from getting dressed to performing physical activities, each of which is coded 0 for “Yes, limited a lot,” 5 for “Yes, limited a little” and 10 for “No, not limited at all”. This yields a score ranging from 100 for the highest level of perceived physical functioning to 0 for being unable to bathe or dress oneself. The SF-36 PF was to be the sole primary outcome as we were primarily interested in change in physical function.

However, during recruitment we noticed that a significant minority of participants scored close to the mean of the general population (ie, normal physical function) so could be considered recovered even before any intervention [43]. This is because they had substantial reductions in functioning in other domains, such as mental or social activity levels [7].

We therefore added a second primary outcome, the CFQ, which is scored as the sum of responses to 11 items related to physical and mental fatigue, each of which is coded 0 for less than usual,” 1 for “no more than usual,” 2 for “more than usual” and 3 for “much more than usual,” where usual is how they felt the last time they were feeling well. This gives us a symptomatic measure of fatigue. The two primary outcome variables are valid and reliable and have been used in previous CFS trials [9,11]. The ethics committee, Research and Development (R & D), and the trial steering and data monitoring committees approved this change (in June 2013) before any outcome data were formally examined. Because of the change from one to two primary outcomes, we reanalyzed our power calculation and plan to recruit more participants (see section on sample size).

The main secondary outcome measure will be the validated self-rated CGI score, which we will use to measure both change in “CFS” and change in “general health” at the end of treatment, compared with baseline. Each will have 7 possible scores from "very much worse" (score of 7) to "very much better" (score of 1)[39]. Both safety and efficacy can be recorded with this item; we will count scores of 1 and 2 (“very much” and “much” better) as positive outcomes, and scores of 6 and 7 (“very much” and “much” worse) as negative outcomes. Scores of 3-5 (“a little” better, no change, and “a little” worse) will be regarded as no change.

#### Safety Measures and Reporting

For safety outcomes, we will include serious adverse events (SAEs), serious adverse reactions to trial treatments (SARs), and serious deteriorations (SDs). SAEs will be defined according to usual clinical trial definitions (ie, an event that is fatal, life-threatening, or results in or prolongs hospitalization; an increase in severe and persistent disability or incapacity; self-harm; or any other important condition that may require medical or surgical intervention to prevent the above [10] and will be reported to the appropriate authorities in the standard manner. SARs are SAEs that are considered to be a reaction to any trial therapy or drug prescribed. SDs will be defined as any of the following outcomes: CGI scores of 6 and 7, active withdrawal from the intervention due to worsening, or a reduction on the SF-36 PF scale by 10 or more points. Participants will record any nonserious adverse events (NSAEs) in their follow-up questionnaire. An adverse event is defined as any clinical change, disease, or disorder recorded by the participant, whether or not it is considered to be related to the trial or its treatments. Participants will be asked to record whether they believe the adverse event was “related to following the GET guide.” In the event of an adverse event (AE), the center leader will judge the seriousness of the event, and, if judged to be serious, the relationship to a trial supplementary therapy or SMC prescribed treatment, and the expectedness of the event. The trial manager will report all SAEs to the principal investigator (PI) within 24 hours, regardless of the relationship to trial treatment. Reporting of SAEs and SARs will be carried out according to normal regulatory research governance requirements.

After an SAE or SAR, the center leader will make a decision as to whether the participant should be withdrawn from either randomized treatment or from the trial, or if an alteration in their SMC is needed; arrangements will be made for further assessment and management as required. The trial manager will provide the center leader with monthly follow-up reports until resolution. These reports will be communicated to the Data Monitoring and Ethics Committee (DMEC), and other appropriate authorities via the trial manager.

A risk assessment has been undertaken and we have concluded that the therapies are of low risk to participants. NSAEs will be reported en bloc to the DMEC on a regular basis, according to the usual regulatory requirements.

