### Hypotheses

First, we will test the null hypothesis that GES plus specialist medical care (SMC) will be no more effective at improving either physical disability or fatigue than usual SMC alone, as shown by no statistically significant difference between the two arms of the trial 12 weeks after randomization. Second, we will test the hypothesis that GES will be acceptable to patients diagnosed as having CFS/ME in specialist secondary care clinics, as demonstrated by less than 25% of eligible patients declining participation in the trial, and more than 75% of those participating being satisfied with the approach. Third, we will assess the difference in the number of participants suffering serious adverse effects, serious adverse reactions, or a serious deterioration across the study arms.

We will also assess whether there is a statistically significant difference in cost-effectiveness between the two interventions, although this is not a hypothesis.

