#### Sample Size

Our original sample size was based upon the SF-36 PF as our primary outcome; however, the significance level was reduced to 2.5% to accommodate 2 primary outcomes [31]. A large previous trial of CFS/ME using the SF-36 PF (the PACE trial) indicated a baseline mean score of 37 (SD 15) and an outcome score of 48 (SD 21) following 12 weeks of practitioner-led GET, an 11-point increase [11]. Based on these previous findings, and our estimate that GES will be less effective than GET, the sample size calculations are based on the assumption that a mean difference of 8 (SD 18) points between intervention arms at the 12-week follow-up will be a clinically useful difference on the SF-36 PF scale after 12 weeks [11]. Thus, assuming a significance level (alpha) of 2.5% and power of 80%, we require a minimum of 98 participants in each group. This sample size will be upwardly adjusted to allow for loss to follow-up and other compliance issues. Based upon previous trials, we expect about 10% loss to trial follow-up [17]; therefore, we will recruit 109 patients in each group (a total of 218).

Based on a previous trial of GET, in which the difference between baseline and 12 weeks was 5.4 points on the CFQ [11], we assume that a mean difference of 3 (SD 6) points will represent a clinically useful difference at the 12-week follow-up. Hence, assuming a significance level (alpha) of 2.5% and power of 80%, we require a total of 174 patients, which is less than the 218 to be recruited, so adequate power will be achieved.

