#### Sensitivity Analysis

Sensitivity analysis will be conducted to assess the impact of missing data on our results. We will estimate whole-scale missing data due to loss to follow-up using multiple imputation by chained equation. This will allow us to conduct a strict ITT for all respondents who took part at baseline. Following recent guidelines, we will also conduct a sensitivity analysis that will take into account the partially nested design of the study and, therefore, assess the potential impact of the “therapist effect” on our results [46]. Further analysis will be conducted to adjust for potential confounders, including sex and age.

A per-protocol analysis will serve as a further sensitivity analysis to investigate the robustness of the conclusions of the primary analysis, following departures from the randomized intervention policies. This will exclude those participants in the control arm who used a GET self-help approach. Subgroup analyses including only those meeting the Oxford or CDC criteria for CFS will also be undertaken. We will analyze moderators of improvement, such as these criteria, but also depression and severity of physical function and fatigue. These subgroup analyses are exploratory and will be interpreted with due caution [47].

#### Analysis for Hypotheses 2 and 3

Chi square will be used to describe any difference in satisfaction (ie, satisfied vs nonsatisfied) across treatment arms and any differences in SAEs, SARs, or serious deterioration (1+ vs none) across treatment arms.

The above plan is what we intend to do; however, the final analyses reported may differ from those planned, allowing for *post hoc* analysis where it is indicated [48]. We will report alternative methods if statistical models do not converge, and omit planned analyses that are superseded, redundant, or no longer of interest. We will report any changes in consequent papers.

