#### 12-Week Follow-Up

The main outcomes, including QALYs, will be measured over the 12-week period from baseline assessment to follow-up. We would expect to see a change in the EQ-5D (which provides us with QALY information) and the WSAS over this time. We will also measure the intervention costs and any short-term impact on the use of other services through the CSRI. We recognize that longer-term impacts, which we are unable to measure may also be important. We will measure serious deterioration using a composite measure including the CGI (“much” or “very much worse”), those who actively withdraw from their intervention, or those whose SF-36 PF score falls by 10 or more points.

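### Serious deterioration is defined in two non-equivalent ways: one counts withdrawal only when due to worsening, the other counts any active withdrawal

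*Protocol article*

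**What the plan says.** Under Hypotheses, the third aim reads: "we will assess the difference in the number of participants suffering serious adverse effects, serious adverse reactions, or a serious deterioration across the study arms". Analysis for Hypotheses 2 and 3 plans a chi-square for "any differences in SAEs, SARs, or serious deterioration (1+ vs none) across treatment arms". Serious deterioration therefore has a planned between-arm comparison. It stands beside serious adverse events (SAEs) and serious adverse reactions (SARs), and the article does not rank the three.

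The composite is set out twice, each time with three components:

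- Safety Measures and Reporting, which is worded as the definition: either of the two worst CGI categories (6 or 7), or else "active withdrawal from the intervention due to worsening, or a reduction on the SF-36 PF scale by 10 or more points".
- 12-Week Follow-Up: the same two CGI categories, "those who actively withdraw from their intervention, or those whose SF-36 PF score falls by 10 or more points".

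Two other places bear on the count. Departure from Intended Treatment states: "The number of participants who actively withdraw from either intervention will be recorded". That covers both arms and mentions a number but no reason. 12-Weeks Post-randomization says of the CGI that "this will be done once for overall health and then a second time specifically for CFS". Neither definition of serious deterioration says which of these two ratings is meant.

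**The concern.** The CGI and SF-36 PF components agree in the two sections. The withdrawal component does not: one section requires worsening as the cause, the other requires no cause. A participant who stops for lack of time or interest is a harm event under one text and not under the other. No sentence gives either text precedence.

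This would matter little if such withdrawals were equally common in both arms. The interventions make that doubtful. The section on SMC Plus GES describes a booklet, an initial appointment and up to three further support appointments, all of which a participant can give up. The section on SMC describes ordinary advice and prescribing, where there is much less to withdraw from. Under the broader definition, withdrawals that have nothing to do with harm could make GES look less safe. If the choice between the texts is made after the counts by arm are known, the safety contrast depends on that choice. The article's Conclusions and Discussion make wider release of the booklet conditional on GES being safe, among other things.

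**Working it through.** **1. Arm size, the only figure in the article that bears on this comparison.** Sample Size states: "assuming a significance level (alpha) of 2.5% and power of 80%, we require a minimum of 98 participants in each group", for a difference of 8 (SD 18). With a two-sided 2.5% level, n = 2 × (2.2414 + 0.8416)² × (18/8)² = 2 × 9.505 × 5.0625 = 96.2, so 97 per arm. The t-test version gives 97.5, so 98. Allowing for 10% loss, 98/0.9 = 108.9, so 109 per arm and 218 in total. The stated figures reproduce.

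**2. Inputs that the article does not give.** It states no expected rate of serious deterioration or of withdrawal, and no significance level for the safety comparison. I assume:

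- a rate b of serious deterioration under the narrower definition, equal in both arms, at 10% or 20%;
- a share w of one arm only withdrawing for reasons other than worsening, at 2%, 5% or 10%;
- independence of these withdrawals from the other components;
- a two-sided 0.05 level.

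**3. Effect of the definition.** Under the narrower definition both arms have rate b and the difference is 0. Under the broader one the affected arm has rate p = b + w(1 − b), so the excess is w(1 − b). Example: b = 0.10 and w = 0.05 give p = 0.10 + 0.05 × 0.90 = 0.145, an excess of 4.5 points, or 0.045 × 109 ≈ 5 extra events.

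**4. Chance that the excess is significant.** Normal approximation: Φ[(p − b − 1.96 × s₀)/s₁], where s₀ is the pooled and s₁ the unpooled standard error. For the example:

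- s₀ = √(2 × 0.1225 × 0.8775/109) = 0.0444
- s₁ = √((0.09 + 0.124)/109) = 0.0443
- Φ[(0.045 − 0.0870)/0.0443] = Φ(−0.95) = 0.17

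| b | w, one arm | p | Excess (points) | P(p<0.05), 109 per arm | P(p<0.05), 98 per arm |
|---|---|---|---|---|---|
| 10% | 2% | 11.8% | 1.8 | 6% | 6% |
| 10% | 5% | 14.5% | 4.5 | 17% | 16% |
| 10% | 10% | 19.0% | 9.0 | 47% | 43% |
| 20% | 2% | 21.6% | 1.6 | 5% | 5% |
| 20% | 5% | 24.0% | 4.0 | 11% | 10% |
| 20% | 10% | 28.0% | 8.0 | 28% | 26% |

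Under the narrower definition the excess is 0 in every row. The chance of a significant result then stays near the nominal level: exact enumeration of the uncorrected chi-square at 109 per arm gives 5.3% at b = 10% and 5.1% at b = 20%.

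**The case against.** The best defence is that Safety Measures and Reporting is the formal definition, and that 12-Week Follow-Up, which comes after the economic evaluation, is a shortened restatement with the qualifier dropped. That is quite possible, and it is a good reason to let the formal wording prevail. It does not remove the conflict, since the later sentence also says how the composite will be measured. The defence can add that the outcome is not primary and that neither the sample size nor the primary analyses are touched. It can also say that CGI categories are compared by arm elsewhere and withdrawals are counted. All of that is fair and limits how far the problem reaches.

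Several stronger readings are tempting, but the document does not support them.

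- *That this is the trial's main harm endpoint.* It is one of three unranked safety outcomes.
- *That the broader text counts only withdrawals from GES.* It refers to each participant's own intervention, and withdrawals are recorded in both arms. An excess in GES is an inference from what each arm offers.
- *That the SF-36 PF component mostly captures random fluctuation.* Take the SDs of 15 and 21 from Sample Size and assume a correlation r of 0.5 or 0.7. The SD of change, √(15² + 21² − 2r × 15 × 21), is 18.7 or 15.0. With a mean change of 0 to +5, Φ[(−7.5 − mean)/SD] gives 20–34% falling by 10 or more. But the same sentence gives a mean change of +11, which yields 16% or 11%. The SD of 21 was also measured after treatment and includes true differences in response.
- *That the chi-square is an error.* No SAE or SAR rate is given. For 4/98 versus 0/98 the uncorrected p is 0.043, the continuity-corrected p is 0.13 and Fisher's p is 0.12, and the article does not say which chi-square is meant. At 98 per arm and event rates of 0.5% to 5%, the uncorrected test has a true size of 0.2% to 4.5%, so there is no inflation. For a composite at 10–20% it is adequate. The handling of sparse tables is ordinary analysis-plan detail.
- *That p>0.05 would be taken as proof of safety.* No section says so.

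**Conclusion.** The contradiction is real and lies in the current text. A safety outcome with a planned between-arm comparison has two definitions that can give different counts and a different contrast. Its size cannot be fixed from the document. Under the stated assumptions it ranges from negligible (2% other-reason withdrawal: an excess below 2 points) to large enough to change the reading (10%: an excess of 8–9 points, with a 28–47% chance of p<0.05). These figures need the other-reason withdrawals to fall in one arm. If they were equal in both arms, the broader definition would raise both counts but create no excess. If they overlap with the other components more than independence implies, the excess is smaller. The unspecified CGI rating is a related, smaller gap in the same definition.

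**What to change.** 1. Use one definition in both sections. The formal wording in Safety Measures and Reporting is the natural choice: withdrawal counts only when worsening is the recorded reason. 12-Week Follow-Up should be amended to match. This concerns how an outcome is counted, not when a participant should stop treatment.
2. In the same correction, state whether the CGI component uses the overall-health rating or the CFS rating.
3. Report each component (CGI 6–7, withdrawal for worsening, SF-36 PF fall of 10 or more) by arm beside the composite, with risk differences and 95% confidence intervals. List withdrawals for other or unknown reasons separately.
4. Settle this before serious deterioration is compared by arm. The article says data analysis is underway, so the report should state when the definition was fixed and whether this was done without sight of the counts by arm.
5. Optional: an exact test for SAEs and SARs if the tables prove sparse.

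The cost is a sentence in each of two sections and one extra table. No new data are needed, provided reasons for withdrawal were recorded. The article mentions recording only the number, so this should be confirmed first.

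### A 10-point fall on SF-36 PF, a primary efficacy scale, is enough for serious deterioration, and only the pooled composite is tested, so it may dilute or offset worsening on the other components

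*Protocol article*

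**What the plan says.** Safety Measures and Reporting defines the composite: "SDs will be defined as any of the following outcomes: CGI scores of 6 and 7, active withdrawal from the intervention due to worsening". The third criterion in that list concerns physical function and is worded "or a reduction on the SF-36 PF scale by 10 or more points". Any one criterion suffices, and the SF-36 PF criterion needs no repeat measurement or agreement from another measure. The 12-Week Follow-Up section restates the composite with the same 10-point rule.

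Primary Outcomes describes SF-36 PF as "scored as the sum of responses to 10 items related to functioning on everyday activities", with items coded 0, "5 for “Yes, limited a little” and 10 for “No, not limited at all". It was first the only primary outcome ("The SF-36 PF was to be the sole primary outcome as we were primarily interested in change in physical function") and is now one of two. Sample Size assumes that "a mean difference of 8 (SD 18) points between intervention arms at the 12-week follow-up will be a clinically useful difference", and Analysis for Hypothesis 1 uses the same 8 points as the cut for individual improvement.

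Analysis for Hypotheses 2 and 3 applies chi-square to "any differences in SAEs, SARs, or serious deterioration (1+ vs none) across treatment arms". It gives no comparison by component.

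**The concern.** Two features combine. First, the SF-36 PF criterion is easy to meet. On a fully answered scale the score moves in steps of 5, so 10 points is two items each dropping one category, or one item dropping two. It is also the first attainable step at or beyond the 8 points that the protocol calls clinically useful, so the same step counts as useful upward and serious downward. A participant who falls 10 points and rates themselves a little worse on the CGI is classed as unchanged on the main secondary outcome and as seriously deteriorated on the safety outcome.

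Second, the criterion is a primary efficacy outcome cut at a point. If GES raises the SF-36 PF distribution, fewer GES participants cross the cut, and that lowers the composite in the GES arm. A single present-or-absent test cannot separate this from what happens on the CGI or withdrawal.

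At stake is the reading of one of the three outcomes under Hypothesis 3. Mixed results are a realistic prospect: the Background sets a trial that found GET effective and safe beside a survey in which 56% of those who had received GET felt worse afterwards.

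**Working it through.** **Planning figures.** The protocol gives no expected rate of serious deterioration, so there is none to reproduce. Its sample size does reproduce. With difference 8, SD 18, two-sided 2.5% and 80% power, n = 2 × 18² × (2.241 + 0.842)² / 8² ≈ 96.2, so 97 per arm, or 98 with the t correction, as stated. Then 98/0.9 = 109 per arm, 218 in total.

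**Inputs.**
- From Sample Size: baseline mean 37 (SD 15), follow-up SD 18 or 21, planned difference 8.
- Assumed, because the protocol does not give them: baseline to follow-up correlation r of 0.5 to 0.8; SMC mean change of 0 to +5; CGI 6-7 rates; and, unless stated, independence of the components.

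**Rate of 10-point falls.** Scores were simulated as bivariate normal, rounded to multiples of 5 and clipped to 0-100. Over the whole grid the SF-36 PF component flags 12-34% of SMC participants. If GES is 8 points better it flags 3-20% of GES participants.

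A closed-form check of the central case (r = 0.6, SDs 15 and 21, SMC change +3), ignoring the floor and using a cut of -7.5 for the 5-point grid:
- SD of change = √(15² + 21² - 2 × 0.6 × 15 × 21) = √288 = 16.97
- SMC: Φ((-7.5 - 3)/16.97) = Φ(-0.619) = 26.8%
- GES: Φ((-7.5 - 11)/16.97) = Φ(-1.090) = 13.8%

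The simulation gives 26.5% and about 13.7%.

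**Share of the composite.** With other components at an assumed 5% in SMC, the central-case composite is 1 - 0.735 × 0.95 = 30%. The part due to SF-36 PF alone is 0.265 × 0.95 = 25%, which is 25/30, or about 83% of events.

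**Direction when CGI 6-7 doubles from an assumed 5% (SMC) to 10% (GES), central case.** The SMC composite is 30% throughout.

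| GES effect on SF-36 PF | GES composite |
|---|---|
| 0 points | 1 - 0.735 × 0.90 = 34% |
| 8 points | 1 - 0.863 × 0.90 = 22% |

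The arms are equal when (1 - p) × 0.90 = 0.735 × 0.95, that is, when the GES rate of 10-point falls is p = 22.4%. In simulation the GES composite is still slightly higher at a 2-point effect and lower at 3 points.

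**Does this need independence?** No. With CGI worsening linked to SF-36 PF change at a latent correlation of 0.3, the 8-point case is about 29% against 21%. At 0.5 it is about 28% against 20%.

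**Dilution with no SF-36 PF effect.** Assume other components at 5% (SMC) and 15% (GES), r = 0.7, SDs 15 and 21, and no mean change. The SF-36 PF component is then 30.9% in both arms.
- Composite: 1 - 0.691 × 0.95 = 34% against 1 - 0.691 × 0.85 = 41%.
- Power with 98 per arm at two-sided 5%: about 17% for the composite, against about 65% for the other components alone.

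**The case against.** The strongest reply is that the protocol does not leave worsening to the composite alone. Analysis for Hypothesis 1 compares the proportions scoring CGI 6-7 across arms, SAEs and SARs are separate outcomes, active withdrawals are counted, and SF-36 PF itself is compared by arm. This largely stands: a doubling of CGI 6-7 would be visible in the planned results. It does not fully answer the point. The CGI model is an ordinal logistic regression over three bands. In its usual proportional-odds form it yields one odds ratio, in which more participants much better can offset more much worse. SAEs and SARs capture a different level of harm, and no between-arm test of withdrawals is stated.

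A sensitive cut is also a defensible precaution for a safety outcome. That stands too, and nothing here shows that 10 points is the wrong threshold.

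A reader might infer three stronger things that the protocol does not support:
- **That a 10-point fall is ordinary score variation, or chance.** Ten points is 0.67, 0.56 and 0.48 of the SDs of 15, 18 and 21, but those describe spread between people. The protocol gives no SD of change and no test-retest figure.
- **That the composite automatically hides harm.** Anyone who meets any criterion is counted, and a true fall in SF-36 PF under GES would raise the composite. The calculation shifts every GES participant equally, so it does not represent a subgroup harmed on that scale. Reversal needs a mean SF-36 PF benefit together with worsening elsewhere.
- **That this component decides the result.** That depends on component rates that the protocol does not give.

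**Conclusion.** The concern holds in a limited form. The rule and the pooled test are as stated, and the SF-36 PF criterion may dominate the composite: about 12-34% of SMC participants flagged by it alone, under assumed correlations of 0.5 to 0.8 and SMC mean changes of 0 to +5.

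The consequence depends on the effect of GES on SF-36 PF. With none, the composite keeps the right direction (30% against 34%) but is diluted. From about 3 points upward it can favour GES while CGI 6-7 doubles. At the planned 8 points it reads 30% against 22%. These figures also rest on the assumed CGI rates of 5% and 10%.

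This is a weakness in how one safety outcome is tested. It does not show that the definition is invalid or that harm would go unseen.

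**What to change.** In Analysis for Hypotheses 2 and 3, keep the composite and its chi-square test. Add that each component (CGI 6-7, active withdrawal due to worsening, SF-36 PF fall of 10 or more points) will be reported and compared by arm with confidence intervals, and that the Hypothesis 3 conclusion will not rest on the pooled composite alone.

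The withdrawal component needs one definition before it can be tabulated. Safety Measures and Reporting limits it to withdrawal due to worsening, while 12-Week Follow-Up counts "those who actively withdraw from their intervention, or those whose SF-36 PF score falls by 10 or more points" with no such limit. The two passages must be reconciled.

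The cost is a few lines of analysis text and one table from data already collected. The downside is fewer events, and so lower precision, for each component than for the composite.
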